### Power calculations

The smallest difference between outcomes between groups is expected to be found in attitudes estimates (a 14% difference in proportions having a positive attitude towards screening [19]) Based on this assumption, power calculations (considering a 5% significance level and an 80% statistical power) indicate that we need to include 200 citizens with lower educational attainment in each group. We expect 47% of citizens invited to CRC screening not to return a stool sample within 45 days. Further, we know that 26% of the population has lower educational attainment [49]. By combining mailed invitations and reminders with telephone calls, we aim to reach a response rate of at least 60% for baseline questionnaire and 80% for follow-up (i.e. study participants). Further, we expect a 50% response rate in the historic study arm. In order to be able to make gender stratified analyses, and considering the rate of screening reminder, rate of lower educational attainment, and questionnaire response rate, we need to include 5000 citizens in each study arm.

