#### Study processes

Seven to 20 weeks before the invitation date, the included citizens in study arms 1 and 2 will receive a link to the baseline questionnaire via their digital mail (with remote printing for exempted citizens). Questionnaire reminders will be sent out after two weeks. Instead of a second questionnaire reminder, non-respondents will be contacted via telephone after four weeks and invited to fill out the questionnaire via telephone interview. In a pilot study, the response rates among lower educational attainment and medium/higher educational attainment citizens using an invitation and a two-week reminder were assessed at 27% and 55%, respectively. The response rates increased to 40% and 64%, respectively, in the two groups, by using telephone interviews. Accordingly, we expect telephone interviews to help reach more of the lower educational attainment citizens. Questionnaire respondents will also be asked for consent to the obtaining and analysis of screening data (date of invitation, reminder, receipt of test in laboratory, and test result) from the screening program database.

Citizens who respond to the questionnaire and give consent to the use of registry data will be randomly allocated into study arms 1 and 2. Allocation will be performed in the ratio 1:1 and will use a computer-generated algorithm for randomization, based on a simple randomization procedure. Randomization will be conducted based on the study participants’ record-ID numbers. Participants will not be able to change study arm after allocation and there will be no blinding.

Citizens who take up screening within 45 days after the screening invitation and citizens with medium or higher educational attainment (i.e. 10 years or more of education) will be excluded from the analyses after randomization. This might cause attrition bias. However, randomization will be conducted externally before screening uptake is known. Furthermore, educational attainment will not be available to researchers at an individual level, unless data are pseudonymized. However, educational level and screening uptake within 45 days of invitation is not expected to be associated with study arm and, hence, no attrition bias is expected.

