### Statistical methods

All statistical analyses will be carried out in Stata/SE 14 (STATACorp LP, College Station, TX, USA). Analyses will be carried out on a 5% significance level, stratified to gender. Estimates will be presented with 95% confidence intervals. Intention-to-treat analyses will be conducted.

Pearson’s chi-square test will be used to test differences in demographic characteristics between respondents and non-respondents as well as between those included in each study arm with lower educational attainment, in order to test for baseline differences. Furthermore, differences in educational attainment and screening uptake within 45 days in each study arm will be compared in order to evaluate the risk of attrition bias.

The main outcome of the trial is informed choice. Informed choice is difficult to measure and the evaluation will be based on adequate knowledge about CRC screening and consistency between attitudes towards CRC screening and screening uptake. This will be judged at group level not individual level. [46] Differences in distributions of responses to knowledge, attitudes, uptake, decisional conflict, and worries in the study arms will be analyzed using the independent sample t-test for continuous variables and Pearson’s chi-square test for categorical variables. The relative risk (RR) will be estimated for uptake using a logistic regression analysis with study arm 2 as the reference comparing to both study arm 1 and the historic cohort. Citizens are defined as having taken up CRC screening if they returned a stool sample within three months after the screening invitation was sent out [47]. For the numeric scale outcomes, a linear regression analysis will be conducted to compare the means between study arms 1 and 2 and study arm 2 and the historic cohort, using study arm 2 as the reference. For ordinal scales, not normally distributed as assessed by histograms and qq-plots, ordinal regression analyses will be conducted, estimating odds ratios for higher scores in study arm 1 and the historic cohort as compared to study arm 2, using study arm 2 as the reference.

Further, generalized linear models from the binary family will be conducted to test if socioeconomic variables (including health literacy) modify the effectiveness of the decision aid on knowledge, attitudes, and uptake. *P* values for these analyses will be estimated using the Wald test.

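### On the plan's own rates, 5000 citizens per arm yields about 147 lower-education citizens per gender, not 200, so the stated 80% power for the planned 14-point difference does not carry over to the gender-stratified analyses

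*Protocol article*

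**What the plan says.** Under Power calculations, the protocol article sizes the trial on "a 14% difference in proportions having a positive attitude towards screening", which it presents as the smallest difference expected among the outcomes. With "considering a 5% significance level and an 80% statistical power", it concludes that "we need to include 200 citizens with lower educational attainment in each group".

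It then moves from people analysed to people invited. It gives 26% for lower educational attainment and states "We expect 47% of citizens invited to CRC screening not to return a stool sample within 45 days". For the questionnaires, "we aim to reach a response rate of at least 60% for baseline questionnaire and 80% for follow-up". Having named gender-stratified analyses, the reminder rate, the education rate and the response rate as considerations, it concludes that "we need to include 5000 citizens in each study arm".

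Three other places bear on this:
- Statistical methods: "Analyses will be carried out on a 5% significance level, stratified to gender".
- Study processes, on the pilot in lower and in medium/higher education citizens: "The response rates increased to 40% and 64%, respectively, in the two groups, by using telephone interviews".
- Study processes also says that early screeners, citizens with medium or higher education, and those who do not return the follow-up questionnaire all leave the analysis.

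**The concern.** The paragraph supplies every rate needed to turn invitations into analysed citizens, so 5000 can be checked directly. If 200 per group is the number for 80% power and the analyses are run separately in men and women, each arm needs 200 of each gender, 400 in all. The stated rates do not deliver that.

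The 60% baseline response also looks like a figure for the whole sample, while only lower-education citizens are analysed, and the pilot found a much lower response among them.

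At stake is how the gender-specific results are read. Someone relying on this paragraph would take an analysis in men or in women to have 80% power for the planned difference. A non-significant result in one gender would then look more informative than it is.

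**Working it through.** **Inputs from the document.** Power calculations: 14-point difference, 5% level, 80% power, 200 per group, 5000 per arm, 26% lower education, 47% without a sample by day 45, 60% baseline response, 80% follow-up response. Study processes: pilot response of 40% (lower education) and 64% (medium/higher).

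**Assumptions.** Two-sided test. Base proportions of 43% and 57%, since the document gives none. Equal gender split. The 5000 are citizens invited: Study population samples 10,000 for the two arms, and only respondents are randomised.

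**1. Reproducing the 200.** For two proportions with mean p̄ = 0.50:

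n = [1.96·√(2p̄(1−p̄)) + 0.8416·√(p1(1−p1) + p2(1−p2))]² / (p2 − p1)²

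With 0.43 and 0.57, n = [1.96 × 0.7071 + 0.8416 × 0.7001]² / 0.14² ≈ 199.04, rounded up to 200. Lower proportions from 0.36 to 0.50 give 196 to 200. The stated 200 therefore fits proportions near 50%.

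**2. Yield at the planned rates.** 5000 × 0.60 × 0.26 × 0.47 × 0.80 = 293.3 per arm, or 146.6 per gender.

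**3. Invitations needed per arm.** The product of the rates is 0.60 × 0.26 × 0.47 × 0.80 = 0.05866.
- 200 per arm, genders pooled: 200 / 0.05866 ≈ 3,410.
- 200 per gender (400 per arm): 400 / 0.05866 ≈ 6,820.
- 400 per arm, ignoring follow-up loss: 400 / (0.60 × 0.26 × 0.47) ≈ 5,456. This still exceeds 5000, and the loss cannot be ignored because follow-up non-responders are excluded.

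So 5000 is more than the pooled comparison needs and less than the gender-stratified one needs.

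**4. The response rate.** Weighting the pilot rates by education gives 0.26 × 0.40 + 0.74 × 0.64 = 0.578, close to the planned 60%. The planned figure thus resembles an all-education rate. With 40%, 5000 × 0.40 × 0.26 × 0.47 × 0.80 = 195.5 per arm, or 97.8 per gender.

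**5. Power for 43% versus 57%.**

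Power = Φ{[0.14·√n − 1.96 × 0.7071] / 0.7001}, with n per comparison group.

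| Baseline response | Non-return by day 45 | Per arm | Per gender | Power, pooled | Power, by gender |
|---|---|---|---|---|---|
| 60% | 47% | 293 | 147 | 93% | 67% |
| 60% | 55% (assumed) | 343 | 172 | 96% | 74% |
| 60% | 60% (assumed) | 374 | 187 | 97% | 78% |
| 40% | 47% | 195 | 98 | 79% | 50% |
| 40% | 55% (assumed) | 229 | 114 | 85% | 56% |
| 40% | 60% (assumed) | 250 | 125 | 88% | 60% |

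**6. What would rescue the 5000.** With the other rates as planned, 400 per arm needs non-return of 400 / (5000 × 0.26 × 0.60 × 0.80) = 64%, or a baseline response of 400 / (5000 × 0.47 × 0.26 × 0.80) = 82%.

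**7. Sensitivity to the base proportion.** At 147 and 98 per gender, power is 68% and 51% for 50% versus 64%, and 82% and 65% for 70% versus 84%. The last pair would need only 141 per group, so it is not what produced the 200.

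**The case against.** **No 80% claim by gender.** The paragraph never says in terms that each gender has 80% power, and 5000 clearly exceeds the roughly 3,410 needed for 200 per arm. The pooled comparison is sound at the planned rates. All of this stands. But gender stratification is given as a reason for the 5000 and Statistical methods stratifies the analyses by gender, so 200 per gender is the natural reading. No other part of the article states a lower requirement.

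**Other outcomes.** A reader might infer that no gender-specific analysis reaches 80% power. The document does not support that. The 67% and 50% belong to a 14-point difference in a dichotomised attitude near 50%. The paragraph calls this the smallest expected difference, and at 147 per gender a difference of about 16.5 points already has 81% power. Attitudes are also to be analysed as a numeric score. If that score were normal and 43% versus 57% lay above a common cut (an assumption), the shift would be about 0.353 SD. That needs about 127 per group, with power by gender of about 85% at 147 and 69% at 98. This objection stands, and it limits the point to the quantity on which the plan was sized.

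**The 50% figure.** It would be tempting to lead with 50%. That figure pairs the lower-education response with a non-return rate for all invited citizens, whereas Background says lower-education citizens participate less. Their non-return is therefore probably above 47%, which helps the yield. At an assumed 55–60%, power by gender is 56–60% with the pilot response and 74–78% with the planned response, still under 80%.

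**Table 1.** One might also argue that the no-difference entry for attitude change contradicts sizing on attitudes. That is weak evidence: the column is headed as the null hypothesis yet contains directional entries, and the paragraph gives its own reason for choosing attitudes.

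**Conclusion.** The arithmetic does not support the stated purpose of the 5000. On the plan's own rates the trial analyses about 293 lower-education citizens per arm and about 147 per gender, against 200. For the planned 14-point difference this means about 67% power within each gender and about 93% pooled. At the pilot's response the expected number is about 195 per arm, with about 79% power pooled and 50% by gender at 47% non-return, or 56–60% by gender at an assumed 55–60%.

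The yields rest on the stated rates; the per-gender numbers add an equal split, and an unequal one makes the smaller stratum weaker. The powers add a two-sided test and proportions near 50%, which the document does not state but which return its 200. The finding concerns the gender-stratified analyses of the difference used for sizing. It does not show that the trial as a whole is too small at its planned rates, or that other outcomes lack power.

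**What to change.** Restate the Power calculations paragraph so that it:

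- gives the expected analysed number as about 293 per arm at the planned response and about 195 at the pilot response for lower-education citizens, with the multiplication shown;
- gives the matching power for the 14-point difference, pooled (about 93% and 79%) and by gender (about 67% and 50%, with the higher figures if a higher non-return is assumed);
- states the base proportion and the non-return rate on which those figures rest;
- drops the implication that 5000 per arm supports gender-stratified analyses at 80% power;
- says that the sample size supports the pooled comparison, and that gender-specific results are to be interpreted as lower-powered.

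No extra recruitment is needed. The cost is a rewritten paragraph with less favourable figures.

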## Discussion

The decision to take up CRC cancer screening is a preference-sensitive choice. The decision is often made without prior contact with healthcare professionals, and hence, comprehensible and accessible information material is crucial. Currently this type of information material is lacking, especially for lower educational attainment citizens, who also have the lowest screening uptake. Our newly developed decision aid is designed to provide lower educational attainment citizens with accessible and comprehensible information to support informed choice about taking up screening. Further, the decision aid is easy to implement directly into the existing screening program, through the national electronic mail system, should it be shown effective on our key outcomes. Preferably, all decisions about screening uptake and non-uptake should be informed. In this trial, we investigate whether non-uptake is informed and can be supported. However, the follow-up questionnaire will be sent out to screening participants as well as non-participants. In a future study, it will be possible to investigate whether screening uptake was informed. By nesting the effectiveness study into an existing screening program using registry data of high quality and with almost 100% coverage [48], the results of this study, combined with future information about the level of informed choices of uptake and non-uptake, may provide a basis for recommendations about targeted information material in CRC screening in particular and guide future information and decision support material in cancer screening in general.

## Abbreviations

CRC: Colorectal cancer
FIT: Fecal immunochemical test
gFOBT: Guaiac fecal occult blood test
IPDASi: International patient decision aid standards collaboration instrument
LEAD trial: Lower educational attainment decision aid trial
RR: Relative risk
